### Key measures

For sub-populations (i) to (viii), the primary exposure is the initiation of OAT with the dispensation of SROM, methadone and buprenorphine/naloxone in an initiator analysis framework. To compare the treatments at key dosing benchmarks, we will follow individuals receiving at least one dispensation of the following dosages per week. The key dosing benchmarks are aligned with BC clinical guidelines and previous literature:[6,58]

**Week 1:** SROM (≤240 mg), methadone (≤40 mg), and buprenorphine/naloxone (≤16 mg/4 mg).

**Weeks 2–3:** SROM (≥140 mg), methadone (≥30 mg), and buprenorphine/naloxone (≥12 mg/3 mg).

**Week 4 and beyond:** SROM (≥480 mg), methadone (≥80 mg), and buprenorphine/naloxone (≥16 mg/4 mg).

For sub-populations (ix) and (x), two treatment groups in per-protocol analysis framework will be defined as follows: individuals who switch to SROM within 30 days of initiating OAT with buprenorphine/naloxone or methadone, respectively, versus those who remain on their initial OAT type. Due to the lack of inpatient information on OAT dosing in our linked database, we will assume OAT receipt prior to hospitalization is continued daily throughout the duration of hospitalization.[6] Time to OAT discontinuation and all-cause mortality will be primary outcomes of interest for the initiator analysis. OAT discontinuation is defined as no OAT dispensation for ≥5 days for methadone and SROM, and ≥6 days for buprenorphine/naloxone. Additionally, time to overdose-related acute care visits (identified using ICD-10 codes T40, T42.4, and T43.6) will be assessed as a secondary outcome. The per-protocol analysis will assess the same set of outcomes: time to all-cause mortality, overdose-related acute care visits and OAT discontinuation.

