**Methods::**

We will conduct a population-level retrospective cohort study using linked data from nine provincial health administrative databases. The study population includes adults (≥18 years) in BC who initiated SROM, methadone, or buprenorphine/naloxone between June 1, 2017, and December 31, 2022. Key sub-populations will include incident users with no prior OAT history and prevalent new users with prior OAT experience stratified by OAT type, stability, and medication switching history. The primary outcomes are time to OAT discontinuation and all-cause mortality, while overdose-related acute care visits will be examined as a secondary outcome. To estimate both the initiator effect and the effect of treatment at guideline-recommended doses, we will apply marginal structural models using inverse probability treatment weighting and ‘clone-censor-weights’ approach to address confounding by indication and time-varying confounding. Sensitivity analyses will evaluate the robustness of our findings, including cohort and timeline restrictions, alternative outcome definitions, and alternative estimation strategies including high-dimensional propensity score and instrumental variable approaches.

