### Study follow-up

The time zero is the first dispensation date of methadone, buprenorphine/naloxone, or SROM. For initiator analysis, follow-up ends at the earliest of outcome, death, loss to follow-up, 24 months after time zero, or December 31, 2022. For per-protocol analysis, we will censor at additional events: (i) treatment switch or falls OAT dose below the key benchmark, and (ii) individuals initiate taper or violate eligibility criteria, such as being pregnant, or incarcerated, or had received cancer or palliative care (see Table 3).

However, for sub-populations (ix) and (x), where treatment is considered a time-varying exposure and individuals may be consistent with both treatment strategies up to 30 days of OAT episode, we will apply the ‘clone-censor-weight’ approach to emulate the per-protocol target trial.[59,60] In this approach, each individual will be replicated into two clones, one for each treatment strategy. When individuals are no longer consistent with the assigned strategy due to a treatment switch, taper initiation, or violation of eligibility, we will artificially censor the corresponding clone at that time. For the clone assigned to the switch to SROM group, individuals will remain uncensored if they switch to SROM within 30 days of OAT episode, and be censored at day 30 if they have not switched by then (see Table 3).

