### Statistical analysis

We will adjust for all baseline covariates to estimate the initiator effect as hazard ratios, differences of cumulative incidence (risk) at 24 month, and risk curves using a marginal structural Cox proportional hazard regression model (MSM) with inverse probability of treatment weighting.[71,72]. For the per-protocol analysis, additional time varying confounding will be adjusted via censoring weights to mitigate selection bias from artificial censoring due to receipt of dose below key benchmark, treatment switching, violation of eligibility criteria including initiating pregnancy, incarceration, or treatment taper. However in the ‘clone-censor-weight’ approach for the sub-population (ix) and (x), we will not artificially censor for the violation of dosing benchmark and will estimate the artificial censoring weights conditional on their covariate history. Sandwich variance estimates will be used to compute the 95% compatibility (confidence) intervals for the adjusted hazard ratios,[73] while 500 bootstrap samples (with replacement) would be used to compute the compatibility intervals for risk differences and compatibility curves for risk curves.[74] We will apply high-dimensional propensity score (hdPS) and instrumental variable (IV) approaches for the initiator analysis as sensitivity analyses.[75,76] While the MSM and ‘clone-censor-weight’ approaches will target the marginal treatment effect, the IV analysis will estimate a local average treatment effect among compliers, i.e., individuals who would be prescribed the treatment preferred by treating physician or facility (see details in IV estimation section later). We will use SAS version 9.4 to prepare analytic data and conduct the statistical analysis using the SAS and R version 4.5.0.

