### Per-protocol analysis

We will conduct a per-protocol analysis to estimate treatment effects under sustained adherence at key dosing benchmarks, complementing the initiator effect.[86] To control the selection bias due to artificial censoring, we will consider two censoring models along with the propensity score models: (i) accounting for treatment switching, receipt of dose below key benchmark, and (ii) accounting for death, loss to follow-up, protocol violation by initiating pregnancy, dose taper, incarceration, or receipt of cancer or palliative care (see Table 3 for outcome specific censoring mechanism). Dose tapering is defined as two consecutive daily dose reductions without an intervening increase. Both censoring weights will be estimated using the approach described in the Initiator analysis section earlier. Final weights will be the product of the stabilized inverse probability of treatment weights at time zero and the post-baseline inverse probability of censoring weights, truncated at the 99th percentile. In the marginal structural model, we will apply a pooled logistic regression approach incorporating the final weights. The fitted model will be used to compute hazard ratios, risk differences, and risk curves. Compatibility intervals and curves will be computed using the approach described earlier. For sub-populations (ix) and (x), the censor-weighting approach will be similar, but we will apply a modified censoring mechanism as described in Table 3.

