## Figures and Tables

**Fig 1. F1:**
[figure not shown]
Construction of treatment episode for opioid agonist treatment for comparing slow-release oral morphine versus methadone and buprenorphine/naloxone

**Table 1: T1:** Key components of the emulated target trials on comparing the initiation of SROM versus methadone and buprenorphine/naloxone to treat people with opioid use disorder using the observational data

Protocol components	Hypothetical target trial	Emulation of the trial from BC health administrative data
Eligibility criteria	Adults aged 18 years or older who initiated OAT with MET, BNX, or SROM between June 1, 2017, and December 31, 2022. Individuals must not be pregnant or incarcerated and have no history of cancer or palliative care.	The same. To identify people who achieve better outcomes from SROM compared to MET and BNX, we will construct ten study populations to emulate the target trials (see Table 2 for details).
Treatment strategies	*For the study population (i) to (viii)* ITT: Initiating OAT with (1) MET, (2) BNX, and (3) SROM. PP: Receipt of at least 1 dispensation of optimal doses*: week 1: MET (≤40mg), BNX (≤16mg/4mg), SROM (≤240mg); weeks 2 through 3: MET (≥30 mg), BNX (≥12mg/3mg), SROM ((≥140mg); week 4 and beyond: MET (≥80mg), BNX (≥16 mg/4 mg), SROM (≥480 mg)[6] *For the study population (ix)* (1) Switching to SROM within 30 days of BNX initiation, (2) Staying on BNX. *For the study population (x)* (1) Switching to SROM within 30 days of MET initiation, (2) Staying on MET.	*For the study population (i) to (viii)* Treatment initiator effect and PP effect of the same strategies as proposed in the target trials. *For the study population (ix) and (x)* Same strategies as defined in the target trials.
Assignment procedures	Randomization. Prescribers, healthcare teams, and individuals are aware of the treatment status.	Individuals will be classified into treatment strategies based on dispensation records. Prescribers, healthcare teams, and individuals are aware of the treatment status.
Time zero	Date of randomization	Date of first OAT dispensation
Outcomes	Time to OAT discontinuation, along with the time to all-cause mortality and overdose-related acute care visit as the secondary outcomes.	Same.

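### In the per-protocol analysis of sub-populations (i) to (viii), one dose within the limit satisfies week 1, so the week-1 upper dose limits are not enforced

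*Protocol article*

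**What the plan says.** Key measures sets weekly dosing benchmarks for sub-populations (i) to (viii) and one rule for meeting them: "we will follow individuals receiving at least one dispensation of the following dosages per week". Table 1 (Treatment strategies) repeats the rule: "Receipt of at least 1 dispensation of optimal doses".

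The benchmarks change direction over time:

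- Week 1, upper limits: "SROM (≤240 mg), methadone (≤40 mg), and buprenorphine/naloxone (≤16 mg/4 mg".
- Weeks 2 to 3, minimums: SROM 140 mg, methadone 30 mg, buprenorphine/naloxone 12 mg/3 mg.
- Week 4 onward, minimums: "SROM (≥480 mg), methadone (≥80 mg), and buprenorphine/naloxone (≥16 mg/4 mg".

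The dosing trigger for artificial censoring is described in four places. Study follow-up gives "treatment switch or falls OAT dose below the key benchmark". Statistical analysis refers to "selection bias from artificial censoring due to receipt of dose below key benchmark". Per-protocol analysis also names only doses below the benchmark. The Table 3 footnote defines mechanism C_3 without a direction, as any departure from the Key measures dosing protocol, with treatment switching included.

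The stated purpose is "to estimate treatment effects under sustained adherence at key dosing benchmarks", and the abstract calls the estimand "the effect of treatment at guideline-recommended doses".

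**The concern.** Requiring at least one qualifying dispensation is a sensible test for a minimum, because one dose at or above the floor shows that the client reached it. It does not work for a maximum, because one dose at or below the ceiling says nothing about the rest of the week. The week-1 limit is breached only if every week-1 dose exceeds it.

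The censoring wording adds a second problem. Exceeding the week-1 limit is not a dose below the benchmark, so three of the four descriptions give no trigger for it. The fourth, C_3, does, but only for clients who fail the Key measures rule.

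Two things are at stake. First, the per-protocol effect is one of the two effects named in the Objective, and the rule lets clients dosed well above the week-1 benchmark count as adherent to it. All-cause mortality and overdose-related acute care are among the outcomes, and the Introduction itself says that methadone needs careful titration because of its long half-life and overdose risk. Second, two analysts following the article could build different per-protocol data sets.

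**Working it through.** The plan gives no figure to reproduce. The check applies the stated rule to week-1 dose sequences. The limits and minimums come from Key measures; the sequences are assumed for illustration, with one dispensation a day for seven days.

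Three versions of a week-1 rule, with limit L and daily doses d1 to d7:

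- Stated rule: keep if any dose ≤ L.
- Starting-dose limit: keep if d1 ≤ L.
- Full limit: keep if every dose ≤ L, that is, if the largest dose ≤ L.

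| Week-1 doses (mg) | L (mg) | Doses over L | Stated rule | Starting-dose limit | Full limit |
|---|---|---|---|---|---|
| Methadone 30×3, 40×4 | 40 | 0 of 7 | keep | keep | keep |
| Methadone 40, then 80×6 | 40 | 6 of 7 | keep | keep | censor |
| Methadone 50, then 40×6 | 40 | 1 of 7 | keep | censor | censor |
| Methadone 50×7 | 40 | 7 of 7 | censor | censor | censor |
| SROM 240, then 480×6 | 240 | 6 of 7 | keep | keep | censor |

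**Size of what is allowed**

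- Methadone: 40 + 6 × 80 = 520 mg, against at most 7 × 40 = 280 mg; 520/280 = 1.86.
- SROM: 240 + 6 × 480 = 3120 mg, against at most 7 × 240 = 1680 mg; 3120/1680 = 1.86.
- Week-4 minimum divided by week-1 limit: SROM 480/240 = 2.0; methadone 80/40 = 2.0; buprenorphine/naloxone 16/16 = 1.0. A client can therefore receive the week-4 dose of SROM or methadone, twice the week-1 limit, from day 2 and remain adherent.
- The two alternative SROM conversions in Table 5 have the same ratio: 640/320 = 2.0 and 320/160 = 2.0.

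**Is the stated rule a starting-dose limit?** No. Methadone 50 mg followed by six days at 40 mg passes it although the first dose exceeds the limit. The taper rule in Per-protocol analysis does not remove this client either: it needs two consecutive daily reductions, and there is only one.

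**Do the censoring descriptions agree?** Take methadone 50 mg on all seven days. No dose meets the limit, so the Key measures rule fails and C_3 in Table 3 censors the client. No dose is below 40 mg, so the trigger in Study follow-up, Statistical analysis and Per-protocol analysis never fires. The same client is censored under one wording and followed under the other.

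**The case against.** **Week 1 may only be meant to show an induction-range dose, with upward titration then allowed.** The article calls the values benchmarks or optimal doses, never maximum doses, and states the rule identically in both places. On this reading, 40 mg then 80 mg is acceptable titration. It is a possible intention, but it leaves the upper limit with almost no effect, and the conflict over a client above the limit all week remains. The article does not settle which form is meant, so the sponsor has to.

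**The BC guideline is not available here.** This stands. The documents cannot show that the guideline treats exceeding these doses within week 1 as a departure. The point rests on the article's own limits and on its own description of the contrast.

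**C_3 already covers it.** This holds in part. Study follow-up and Per-protocol analysis both point to Table 3, and C_3 catches a client whose every dose is too high. But C_3 takes its content from the Key measures rule, so one compliant dose still clears the week.

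**No magnitude is shown.** This also stands. The sequences are invented, and no week-1 dose distribution is given. The exposure is one week of a follow-up of up to 24 months.

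**A strict limit would censor rapid titrators.** This is a fair cost. The Introduction says that people using fentanyl may need higher doses, so an every-dispensation limit could remove clients of particular interest. It is a reason to choose the form deliberately.

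**Coding detail belongs in the analysis plan.** Nothing is said to be missing. The article states the rule twice and the trigger four times; the rule does not enforce an upper limit, and the trigger descriptions disagree.

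**Conclusion.** The concern holds. As written, the week-1 values do not act as upper limits on dosing or on the starting dose, and three of the four censoring descriptions give no trigger for exceeding them. The week-1 part of the per-protocol strategy therefore does not match its description as treatment at guideline-recommended doses under sustained adherence.

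The scope is narrow: week 1 of the per-protocol analysis in sub-populations (i) to (viii), across its three outcomes and the Table 5 dose variants. The initiator analysis is unaffected, as are sub-populations (ix) and (x), where dosing violations are not censored. In the illustrative sequences, 6 of 7 doses can exceed the limit and the weekly total can reach 1.86 times the intended maximum. How many clients are affected, and which way any bias would run, cannot be determined from the document. This should be corrected before analysis; it does not invalidate the design.

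**What to change.** Define the C_3 dosing trigger once: any week-1 dispensation above the week-1 limit, or, from week 2 on, any week with no dispensation reaching that week's minimum. If only a starting-dose limit is intended, the first part becomes a first dispensation above the week-1 limit. The sponsor's clinicians should decide which is meant.

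Then refer to deviation from the benchmark, in place of a dose below it, in Study follow-up, Statistical analysis and Per-protocol analysis. Align Key measures and Table 1 with the definition, and apply the same trigger to the Table 5 dose variants.

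The cost is wording and one recoded week-1 flag. Study status and timeline says that no analysis has been done. Study design already plans to identify dispensation dates and doses, and the taper rule already uses daily doses. The every-dispensation form adds some artificial censoring in week 1, which the C_3 weights must handle. Because time-varying covariates are lagged by one week, those week-1 weights rest on baseline information. The first-dispensation form censors fewer clients.

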### Study status and timeline

The de-identified administrative health data from June 1, 2017 to December 31, 2022 has been obtained, but no analyses have been conducted to date. Data cleaning, cohort construction, and all planned analyses will begin following protocol approval and the study is expected to be completed within six months afterwards.

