Follow-up	Intention-to-treat (ITT): from time zero to outcome, death, loss to follow-up, 24 months after time zero, or December 31, 2022, whichever occurs first. Per-protocol (PP): additionally, we will assess adherence weekly and censor follow-up at protocol violation (see Table 3).	Same.
Causal contrasts	ITT for the sub-populations (i) to (viii) and PP for all.	Treatment initiator analysis for the sub-populations (i) to (viii), and PP for all.
Analysis plan	ITT: Hazard ratios will be estimated using Cox PH model. To obtain risk curves and risk differences at 24 months, we will estimate the baseline hazard and combine it with covariate effects to compute cumulative risks. To adjust for potential selection bias due to loss to follow-up, we will use inverse probability weighting (IPW) as a function of baseline and time-varying covariates. PP analysis: same except that individual are censored at non-adherence and uncensored individuals are assigned IPW that are a function of baseline and time-varying variables.	*For the study population (i) to (viii)* Initiator analysis: Marginal structural models with treatment weights from propensity scores models and censoring weights due to loss to follow-up. Weights will be estimated as a function of baseline and time-varying covariates. PP: Same as initiator analysis except potential pre- and post-baseline confounders that are associated with adherence to the treatment strategies will be included in the censoring models. *For the study population (ix) to (x)* Same PP analysis as applied to the study population (i) to (viii), except that individuals’ clone are used with a modified censoring mechanism (see Table 3).

* The optimal SROM doses are determined applying 1:6 MET-to-SROM conversion rate as per BC guidelines.[6]

**Table 2: T2:** Target study populations for comparative effectiveness analysis

Study population	Definition	Rationale
Incident users	(i) No history of OAT dispensation, dating back to January 1, 1996	To evaluate treatment outcomes among individuals initiating OAT for the first time
Prevalent new users	(ii) No dispensation for ≥5 days of methadone and SROM and ≥6 days for buprenorphine/naloxone	To capture repeated OAT attempts after a washout period, reflecting common real-world patterns.

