Treatment switch		C_3_		C_3_		C_3_
The overdose-related first acute-care visit					outcome	outcome

a. end of study follow-up is either Dec 2022 or 24 months from time zero, whichever occurs earlier C_1_, C_2_, and C_3_ indicate different censoring mechanism: C_1_: censoring due to end of study follow-up; C_2_: censoring due to death (not the all-cause mortality outcome), loss to follow-up, deviation from the trial exclusion criteria such as initiation of pregnancy, incarceration, dose taper, cancer or palliative care, leaving out of BC. Dose taper will be defined as two consecutive daily dose decreases (without intervening increase); C_3_: censoring due to deviation from the dosing protocol as mentioned in the key measures section, including treatment switching. Censoring for violating dosing protocols will not be applied to the study sub-populations (ix) and (x), as defined in Table 2. For the clone designated for switching to SROM in these sub-populations, individuals will be censored at day 30 if they remain on the initial OAT beyond 30 days, but will not be censored if they switch to SROM within 30 days of initiation; Separate censoring models will be used for C_2_ and C_3_.

**Table 4. T4:** Time fixed and time-varying covariates to estimate the inverse probability of treatment and censoring weights

Variable	Category	How the variable is defined and measured
*Socio-demographic factors*		
Age	Continuous	Based on birth date information from the client registry.
Sex	Male/Female	Based on medical records that record sex.
Living in rural region	Yes/No	Based on the population of the assigned local health area[65]
Homelessness/unstable housing in past 5 years^‡^	Past year, Past 1–5 years, Never/>5 years	Defined through International Classification of Diseases (ICD) 10: Z59.0, Z59.1 from physician billing or hospital discharge records or 3 consecutive records of no fixed address from Social Development and Poverty Reduction (SDPR)
Incarcerated in past year^‡^	Yes/No	Admission to BC correctional facilities and identified through records in the past year from the provincial corrections database.
Receipt of income assistance in the past year^‡^	Yes/No	Identified through records in SDPR and PharmaCare plan information on medication dispensations, using records within the past year.
Calendar year of time zero	2010 to 2022	Determined based on the dispensation date from PharmaNet.
*Comorbidity*		

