**Variable definition**		
Alternative optimal doses using 1:8 and 1:4 from MET to SROM conversion rate.[5,9]	1. Week 1: SROM (≤320 mg), MET (≤40 mg), and BNX (≤16 mg/4 mg); Weeks 2–3: SROM (≥240 mg), MET (≥30 mg), and BNX (≥12 mg/3 mg); Week 4 and beyond: SROM (≥640 mg), MET (≥80 mg), and BNX (≥16 mg/4 mg). 2. Week 1: SROM (≤160 mg), MET (≤40 mg), and BNX (≤16 mg/4 mg); Weeks 2–3: SROM (≥120 mg), MET (≥30 mg), and BNX (≥12 mg/3 mg); Week 4 and beyond: SROM (≥320 mg), MET (≥80 mg), and BNX (≥16 mg/4 mg).	PP
OAT discontinuation: 14 days	Alternative discontinuation thresholds have been defined in other studies.[88]	Both
OAT discontinuation: 30 days		Both
Outcome: all-cause acute care visits	In 2023, opioid-related poisonings resulted in 17 hospitalizations and 78 ED visits per day in Canada, marking a 16% increase compared to 2022.[89] Repeat ED visits (two or more) for OUDs within a year rose from 26% to 34% between 2018 and 2022 in Alberta, Ontario, and the Yukon.[90] Time to all-cause acute care visits will be considered as another outcome. We will repeat the statistical analysis for this outcome to evaluate the impact of alternative outcome on our results. Other components of the target trial and emulation process will remain the same.	Both
No truncation at 24 months of follow-up	While this redefining follow-up may cause instability in the weights of statistical analysis, the non-truncation at 24 months is to confirm the results.	Both
Alternative definition of prevalent new users: (i) no OAT dispensation in past 14 days, and (iii) no OAT dispensation in past 30 days, and (iii) no OAT dispensation in past 90 days.	To account impact of alternative definition of prevalent new users on our results. Three study population will be defined accordingly to assess the impact of eligibility criteria.	Both
No episode discontinuation at dose tapering ^f^	To include periods of time in which individuals wished to reach a state of abstinence.	PP
No episode discontinuation at receiving cancer or palliative care	To include individuals discontinuing treatment after receiving cancer or palliative care	PP
Composite outcome: Overdose-related acute care visits or OAT discontinuation	Instead of considering separate outcomes of overdose-related acute care visits and OAT discontinuation, we will consider the composite outcome of any of the two events. The other components of emulation will remain the same.	Both
Model specification		

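### The weeks 2–3 SROM benchmark (≥140 mg) breaks the plan's own 1:6 methadone-to-SROM rule, which gives 180 mg, so on that rule SROM faces a laxer per-protocol dose threshold than methadone

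*Protocol article*

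**What the plan says.** The protocol article sets weekly dose benchmarks for three periods, and a client meets them with at least one qualifying dispensation per week. For weeks 2–3, Key measures gives "SROM (≥140 mg), methadone (≥30 mg), and buprenorphine/naloxone (≥12 mg/3 mg"). Table 1, under Treatment strategies, gives the same values: "weeks 2 through 3: MET (≥30 mg), BNX (≥12mg/3mg), SROM ((≥140mg").

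The Table 1 footnote, marked at the head of the dose list and so covering all three periods, gives the source of the SROM values: "The optimal SROM doses are determined applying 1:6 MET-to-SROM conversion rate as per BC guidelines".

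Table 5 (Variable definition) adds two sensitivity sets, at 1:8 and 1:4. Their weeks 2–3 entries are "Weeks 2–3: SROM (≥240 mg), MET (≥30 mg), and BNX (≥12 mg/3 mg") and "Weeks 2–3: SROM (≥120 mg), MET (≥30 mg), and BNX (≥12 mg/3 mg").

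The benchmarks decide who is censored. Study follow-up lists, among the extra per-protocol censoring events, "treatment switch or falls OAT dose below the key benchmark". Table 3 codes this as C3 for all three outcomes. Its footnote limits the scope: "Censoring for violating dosing protocols will not be applied to the study sub-populations (ix) and (x), as defined in Table 2".

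**The concern.** The footnote and the weeks 2–3 cell cannot both be right. If SROM doses are methadone doses times six, the cell should read 180 mg. If 140 mg is intended, the footnote is wrong for that period.

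This matters because the cell is a working threshold. In sub-populations (i)–(viii) it fixes which SROM clients count as adherent during titration, in a direct comparison with methadone. If the SROM threshold is lower on the plan's own equivalence scale, the two arms have different adherence rules in those weeks. Censoring ends follow-up, so the effect can outlast the two weeks. A methadone client censored in week 2 or 3 loses all later person-time, while an SROM client at the equivalent dose who reaches 480 mg by week 4 can contribute up to 24 months.

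The plan is also ambiguous to code. A programmer working from the footnote would use 180 mg and one working from Key measures would use 140 mg, giving different per-protocol cohorts from the same protocol.

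**Working it through.** **Inputs.** Methadone benchmarks of 40, 30 and 80 mg and main SROM benchmarks of 240, 140 and 480 mg (Key measures and Table 1); the 1:6 ratio (Table 1 footnote); the 1:8 and 1:4 sets (Table 5).

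**Formula.** SROM benchmark = methadone benchmark × ratio.

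| Set | Week 1 (methadone 40) | Weeks 2–3 (methadone 30) | Week 4+ (methadone 80) |
|---|---|---|---|
| Main, 1:6 | 40 × 6 = 240; stated 240 | 30 × 6 = **180; stated 140** | 80 × 6 = 480; stated 480 |
| 1:8 | 40 × 8 = 320; stated 320 | 30 × 8 = 240; stated 240 | 80 × 8 = 640; stated 640 |
| 1:4 | 40 × 4 = 160; stated 160 | 30 × 4 = 120; stated 120 | 80 × 4 = 320; stated 320 |

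Eight of the nine values reproduce exactly. Only 140 mg does not.

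**Size of the gap.**
- Implied ratio: 140 / 30 = 4.67.
- Shortfall: (180 − 140) / 180 = 22%, or 40 mg.
- Methadone equivalent at 1:6: 140 / 6 = 23.3 mg, against the 30 mg required of methadone clients.

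**Clients affected.** SROM clients whose highest dose in a week is 140–179 mg stay uncensored. Methadone clients at 23.3 to just under 30 mg are censored.

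**Spread of the sensitivity sets.**
- Around 140 mg: 120/140 − 1 = −14% and 240/140 − 1 = +71%.
- Around 180 mg: 120/180 − 1 = −33% and 240/180 − 1 = +33%.
- Week 1: 160/240 − 1 = −33% and 320/240 − 1 = +33%.
- Week 4+: 320/480 − 1 = −33% and 640/480 − 1 = +33%.

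The two sets are symmetric around 180 mg, not around 140 mg.

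**Step up to week 4.** Methadone: 80/30 = 2.67-fold. SROM as stated: 480/140 = 3.43-fold. SROM at 180 mg: 480/180 = 2.67-fold, the same as in both sensitivity sets (320/120 and 640/240). These last two comparisons follow from the single mismatch and are not separate evidence of harm.

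**The case against.** The mismatch itself is hard to dispute: 140 mg appears in both text and table, and the footnote covers all periods. The case on the other side concerns what follows from it.

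- **Laxer only at 1:6.** At 1:4, 140 mg SROM equals 140/4 = 35 mg methadone, which is stricter than 30 mg. At 1:8 it equals 140/8 = 17.5 mg, which is laxer. The implied 1:4.67 lies within the plan's own sensitivity range. This stands: the inequality is relative to the 1:6 rule that the plan adopts for its main analysis.
- **140 mg may be deliberate.** Key measures also says the benchmarks follow BC guidelines and earlier literature, and neither source can be seen here. The exact 1:8 and 1:4 values point to a slip but do not prove one. This also stands. If 140 mg is intended, the footnote needs the correction.
- **A different threshold is not in itself a bias.** Benchmarks define strategies, need not be equipotent, and C3 censoring has its own weight model. That is fair, but weights adjust for selection under a given strategy. They cannot reconcile a strategy that the plan describes in two ways.
- **Narrow reach.** From week 4 every SROM client needs at least 480 mg, so anyone still at 140–179 mg is censored then. That limits the impact. Clients who pass through the band and reach 480 mg in time still keep follow-up that equivalent methadone clients lose.
- **The sensitivity sets cover both values.** 120 and 240 mg lie either side of 140 and 180 mg. They do not show which value the main analysis should use.

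**Conclusion.** The concern holds. The weeks 2–3 SROM benchmark contradicts the plan's stated conversion by 40 mg (22%), and either the cell or the unqualified footnote is wrong. Taking 1:6 as the equivalence, the SROM arm has the laxer dose-censoring rule against methadone in those two weeks.

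The scope is the per-protocol analysis of sub-populations (i)–(viii). The initiator analysis, sub-populations (ix) and (x), and the week 1 and week 4+ thresholds are unaffected. No such inequality can be claimed for buprenorphine/naloxone, because the plan states no conversion for it. The document does not say how many clients fall in the 140–179 mg band, so neither the size nor the direction of any bias can be computed. It should be fixed because it is an operational threshold, but it does not undermine the study as a whole.

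**What to change.** Before the per-protocol cohort is coded, settle which statement is intended:

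- **If the 1:6 rule is meant to hold throughout:** restate the weeks 2–3 SROM benchmark as ≥180 mg in Key measures and in Table 1.
- **If 140 mg is a deliberate guideline value:** keep it, amend the Table 1 footnote to exempt weeks 2–3, and cite the source of 140 mg.

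The cost is one value in two places, or one footnote, plus one line of code to check. The article reports that "no analyses have been conducted to date", so the change can be made without knowledge of results. Made later, it would be a post hoc change to an adherence rule.
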